## Abstract

**Background:**

Pain is one of cancer patients’ most frequent and distressing symptoms; however, analgesics’ side effects often increase symptom burden. Further, with the home rapidly becoming the primary cancer care setting, family caregivers (FCs) commonly play central roles in patients’ pain self-management, but with little or no preparation. One US-tested intervention, the PRO-SELF© Plus Pain Control Program (PCP), designed to support cancer outpatients and their FCs in pain self-management, is currently being tested in the Swiss multi-centre PEINCA study. The current PEINCA-FAM study is a sub-study of PEINCA. The aims of PEINCA-FAM are: a) to test the efficacy of the adapted German PRO-SELF © Plus PCP to reduce side effects of analgesics; b) to enhance patients’/FCs’ knowledge regarding cancer pain; and c) to explore FCs’ involvement in patients’ pain self-management.

**Methods:**

This mixed methods project combines a multi-centre randomized controlled clinical trial with qualitative data collection techniques and includes 210 patients recruited from three oncology outpatient clinics. FCs involved in patients’ pain self-management are also invited to participate. After baseline evaluation, eligible participants are randomized to a 6-week intervention group and a control group. Both groups complete a daily pain and symptom diary. Intervention group patients/FCs receive the weekly psychoeducational PRO-SELF© Plus PCP interventions; control group patients receive usual care. After completing the six-week study procedures, a subsample of 7–10 patients/FCs per group and hospital (*N* = 42–60) will be interviewed regarding their pain management experiences. Data collection will take place from April 2016 until December 2018. An intent-to-treat analysis and generalized linear mixed models will be applied. Qualitative data will be analysed by using interpretive description. Quantitative and qualitative results will be combined within a mixed method matrix.

**Discussion:**

In clinical practice, specially trained oncology nurses in outpatient clinics could apply the intervention to reduce side effects and to enhance patients’/FCs’ self-efficacy and pain management knowledge.

**Trial registration:**

The PEINCA study is registered in the Clinical Trials.gov site (code: NCT02713919, 08 March 2016).

## Background

### Cancer pain and analgesics’ side effects management

Pain is one of cancer patients’ most frequent and distressing symptoms. However, analgesics’ side effects often increase symptom burden [1, 2]. The International Association for the Study of Pain defines pain as “an unpleasant sensory and emotional experience associated with actual or potential tissue damage, or described in terms of such damage” [3]. World Health Organization (WHO) guidelines note that the main focus of pain management is analgesics. As depicted in Table 1, these guidelines focus on a 3-step progression of analgesics from non-opioids to strong opioids, which are associated with burdensome side effects [4, 5]. For opioids, the most common of these side effects are constipation, nausea, emesis, and concentration difficulties; the most feared, though very rare, are respiratory depression and death. However slight the risk, fear may still lead to early discontinuation, underdosing, or otherwise inadequate analgesia [6, 7].

**Table 1 Tab1:** Categorization of pain, appropriate analgesics, side effects, and co-medication

WHO analgesic ladder steps	Score 0/10 on NRS	Category of analgesic	Most important analgesic	Most important side effects	Co-medication
1 (mild pain)	< 3	Non-opioids	- Nonsteroidal Anti-Inflammatory Drugs (NSAIDs)	- gastrointestinal complications - heart attack - stroke - skin or allergic reactions	- Proton pump inhibitor - Antihistamines - Corticosteroids
			- Acetaminophen - Metamizole	- renal and liver toxicities - Hepatotoxicity - skin or allergic reactions	- Antihistamines - Corticosteroids
2 (mild to moderate pain)	3–6	Weak opioids ± Non-opioids	- Tramadol - Tilidine + Naloxone	- Constipation - Nausea - Pruritus - motor and cognitive impairment - respiratory depression - sedation	- Laxatives - Anti-emetics - Corticosteroids - Antihistamines - Major tranquillizers - Psychostimulants
3 (moderate to severe pain)	> 6	Strong opioids ± Non-opioids	- Morphine - Hydromorphone - Oxycodone - Methadone - Levorphanol - Pethidine		

Note. Categorization of pain, appropriate analgesia, side effects and co-medication according to the WHO-sequential three-step analgesic ladder [5–7, 63, 70, 71]

Abbreviations: *WHO* World health organization, *NRS* Numeric rating scale, *NSAIDs* Nonsteroidal anti-inflammatory drugs

Although pain is a treatable symptom, up to 40% of cancer patients experience inadequate pain management. System-level barriers include limited access to pain specialists or opioids [8] and misconceptions of healthcare professionals (e.g., misconceptions and knowledge gaps concerning pain management [9]). Patient-level barriers can be divided into four groups: cognitive (e.g., lack of information), affective (e.g., stress, anxiety, depression), sensory (e.g., analgesics’ side effects) and practical (e.g., implementing pain management in everyday life) [10]. Family caregivers (FCs) directly involved in patients’ pain management commonly experience the same barriers as the patient. FCs are defined as relatives, partners, friends, or neighbours who provide care to patients [11].

With the home becoming the primary setting for many aspects of cancer care, a key goal is to improve patients’ pain and side effect self-management [12]. Self-management consists largely of strategies for solving problems, making decisions, taking action, utilizing resources, forming patient/healthcare provider partnerships, and dealing with physical and psychological issues to avoid or delay deterioration [13, 14]. FCs commonly play central roles in patients’ pain self-management. However, while FCs may administer medications, implement pain relief strategies, and provide emotional support [10, 15], they often assume their tasks with little or no preparation, knowledge, resources, or skills [16]. The psychological and physical costs include a high prevalence of anxiety and depression, social isolation, sleep disturbances, fatigue, and even an elevated risk of coronary heart disease [17–19]. The responsibility for pain management without corresponding skills often results in FCs’ loss of self-efficacy [20]. Self-efficacy is defined as the confidence in one’s ability to perform the behaviours necessary to achieve a target outcome [21]. Recent studies on cancer pain management reveal that high self-efficacy improves both patients’ well-being and FCs’ mood [22, 23]. However, little research has focused on FCs’ influence and self-efficacy vis à vis supporting self-management of pain and analgesics’ side effects in cancer outpatients.

### Supporting self-management of pain and analgesics’ side effects

Three recent meta-analyses focusing on the effects of psychosocial interventions to support cancer pain management from 1983 to 2012 found that, while gaining attention, the psychosocial approach to pain management remains understudied [24–26]. The two most common intervention types were skill training and education [25]. Regarding the main outcome measures, i.e., effects on pain intensity, pain interference in daily activities, knowledge, and attitudes towards cancer pain and analgesics, these meta-analyses revealed various significant, though moderate overall improvements. Further, a systematic evaluation of interventions’ content, structure, and efficacy to improve patients’ self-management of cancer pain revealed no discernible patterns with respect to components, duration, or delivery type or mode [27]. We found no studies that focused on the side effects of analgesics.

To date, little research has focused on interventions supporting FCs in patients’ cancer pain self-management. First, Keefe et al. [28] tested the feasibility of a partner-guided cancer pain management training program with 78 end-of-life patients and their FCs. Intervention group FCs showed significantly higher levels of self-efficacy regarding support for the control of pain and other symptoms. Second, in a randomized controlled trial (RCT) of caregiver assisted coping skill training for cancer patients and their FCs, Porter et al. [29] reported significant results compared with an education program. Additionally, enhanced knowledge of cancer pain management led to both decreased anxiety symptoms in both groups and increased symptom management self-efficacy in FCs. However, as this study lacked a standard care control condition, these results should be interpreted with caution. Third, Hendrix et al. [23] tested an individualized training intervention on self-efficacy in 120 patient-caregiver dyads. FCs in the intervention group demonstrated significant increases in self-efficacy regarding pain control, prevention of infections, maintenance of nutrition, and practical home care issues.

However, no studies have evaluated the effectiveness of interventions focusing on analgesic side effect management to improve self-management in cancer patients and their FCs. Similarly, no study has yet investigated correlations between FCs’ cancer pain management knowledge and self-efficacy related to pain management and patients’ pain intensity.

### The PRO-SELF© plus pain control program, PEINCA and PEINCA-FAM

One psychoeducational intervention included in the above-noted meta-analyses, the PRO-SELF © Pain Control Program (PCP), an intervention to support self-management of pain in adult oncology outpatients and their FCs, showed statistically significant and clinically meaningful reductions compared to standard care in both average and worst-pain intensity in a large RCT (*N* = 174) [30]. In further research, the intervention was expanded regarding its duration (from 6 to 10 weeks) resulting in the PRO–SELF © Plus PCP [31, 32]. Koller, Miaskowski, De Geest, Opitz, and Spichiger [33] translated and adapted this version for use in German-speaking populations. A pilot RCT using 39 oncology outpatients yielded a statistically significant increase in test subjects’ knowledge and demonstrated this version’s feasibility. Based on the pilot RCT’s findings, the intervention was adapted and is currently being tested within the multi-centre “Mixed methods study to test the efficacy of the adapted German PRO–SELF © Plus PCP, an intervention directed at outpatients with cancer and their family caregivers to reduce pain and related symptoms” (PEINCA) in Switzerland. The overall aim of the multi-centre mixed methods PEINCA study is to evaluate the efficacy of the adapted German PRO-SELF© Plus PCP, which was designed to improve outpatients’ and their FCs’ management of pain and pain intensity. The purpose of this sub-study of PEINCA is to test the efficacy of the adapted German PRO-SELF © Plus PCP at both reducing analgesic side effects and enhancing cancer patients’ and FCs’ knowledge of cancer pain as well as to explore their learning processes. In addition, FCs’ involvement in patients’ pain self-management and association between their self-efficacy and knowledge of cancer pain with the cancer patients’ pain intensity will be investigated (PEINCA-FAM).

### Theoretical framework

The overall framework of the PRO-SELF © Plus PCP was the Theory of Symptom Management (TSM) [34]. A further development of the TSM, the Symptom Management Model (SMM, see Fig. 1), which depicts interacting concepts, serves as the theoretical framework for this study [35]. Precipitating factors (antecedents) such as demographic, sociocultural and psychological characteristics, can influence perceived symptoms at baseline (intercepts) and over a given trajectory (slope). By charting the trajectories of symptoms in relation to interventions (symptom management strategies) and patient/FC/nurse interactions, we can illustrate these interactions’ continued influence over patients’ and their FCs’ outcomes (consequences). In this study, consistent with the SMM, cancer pain is viewed as a complex, multidimensional experience frequently accompanied by analgesics’ side effects. Precipitating factors, e.g., social environments and lack of knowledge, influence symptom trajectories. Within the framework’s symptom management strategy, our intervention focuses on supporting cancer patients’ pain and analgesic side effect self-management and the involvement of FCs. Patients as well as FCs are seen as key players who interact with intervention nurses. Alongside improved knowledge of cancer pain and self-efficacy in FCs, reduction of analgesics’ side effects is a key intervention outcome.

**Fig. 1 Fig1:**
[figure not shown]
Diagram of the Symptom Management Model. *Note.* The Symptom Management Model (SMM) [35]. Abbreviation: QoL = quality of life. Copyright © gratefully received by Copyright Clearance Center’s RightsLink® service/ John Wiley and Sons

In addition, Bandura’s Social Cognitive Theory (SCT), an adult learning theory, provided the supplementary conceptual framework for the intervention [36]. SCT acknowledges that learning is a cognitive process that takes place in a social context and can occur through processes of observation, with each individual possessing a self-regulating system that affects motivation and learner differentiation. As part of this system, Bandura introduced the concept of self-efficacy [37], along with major influencing factors: mastery experiences, live modelling, performance exposure and positive appraisal [21]. Through our intervention to educate cancer patients and their FCs, we aim to develop their knowledge regarding pain management, their self-efficacy regarding pain management, and their symptom self-management skills. This entails keeping a diary, setting goals and establishing a management plan to reach those goals.

### Aims

PEINCA-FAM aims to test the adapted German PRO-SELF © Plus PCP pain self-management intervention to reduce cancer outpatients’ analgesics’ side effects, to explore patients’ and FCs’ knowledge of cancer pain and their learning processes, and to investigate FCs involvement in patients’ pain self-management and associations between their self-efficacy, knowledge of cancer pain and patients’ pain intensity. Specific aims of this study are: (1) to test the efficacy of the adapted German PRO-SELF © Plus PCP to reduce analgesics’ side effects by focusing on constipation, nausea, emesis and concentration difficulties; (2) to test the efficacy of the adapted German PRO-SELF © Plus PCP to improve knowledge of cancer pain management in patients and FCs and to qualitatively explore patients’ and FCs’ learning process during the intervention; and (3) to explore the association between FCs’ self-efficacy and knowledge of cancer pain with patients’ pain intensity and to qualitatively explore FCs’ influence on patients’ pain self-management.

## Methods

### Study design

Embedded in the ongoing PEINCA study, the PEINCA-FAM sub-study applies a mixed method approach. In a concurrent embedded strategy, an RCT is combined with qualitative parts [38, 39]. All data are generated within PEINCA. The following describes the PEINCA study’s essential methods as they apply to PEINCA-FAM.

### Sample and setting

Patients with cancer pain are recruited from oncology outpatient clinics at three university hospitals in the German speaking part of Switzerland. These individuals are included if they (1) are aged ≥18 years; (2) have experienced any type of recurrent cancer pain, i.e., rated ≥3 on a 0–10 Numeric Rating Scale (NRS, 0 = no pain, 10 = worst imaginable) over the past week; (3) have an estimated life expectancy of > 6 months; (4) are able to understand, read and write German; and (5) have access to a telephone. Participants are excluded if they (1) have cognitive dysfunction or hearing impairment; (2) are hospitalized > 2 weeks during the study; and (3) are suffering solely from neuropathic pain. To be eligible, FCs must be (1) aged ≥18 years; (2) able to understand, read and write German; and (3) willing to participate in all intervention sessions.

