### Recruitment

Specifically trained nurses from the outpatient clinics work as research assistants (RAs) for the study. All RAs are experienced registered nurses or graduate students in nursing who have received study-specific training by the study coordinator (HR). RAs screen potential participants and verify inclusion criteria via patient files and discussions (regarding life expectancy, etc.) with their treating physicians. If the initial inclusion criteria are met, the RAs contact the patients directly during their outpatient appointment to check whether they have experienced repeated pain that they would rate on an NRS as ≥3 over the last week, are able to understand, read and write German, and have access to a telephone. The RAs then inform patients about the study and invite them to participate. Each patient is also asked if an FC is involved in their daily pain self-management. If yes, the FC is also invited to participate in the study. Written information and consent forms (including those for FCs, if necessary) are then given to the patient. After at least 24 h, an RA contacts each patient (or patient/FC dyad) again to provide verbal information to the FC as needed, ask about their decision regarding participation, and collect the signed written consent form. In all settings, these written informed consent forms are stored safely in the Investigator Site File (ISF) by the RAs. Only afterwards are participants randomized to the IG or CG. Patients and FCs have the right to withdraw from the study at any time without consequences.

Concerning the recruitment of participants for qualitative data collection, all patients (and FCs) are asked at the beginning of the main study whether they are willing to participate in an interview following completion of the study’s 6 weeks of procedures. At the end of the final home visit, the intervention nurse (IN) or an RA asks selected patients (and FCs) whether they are still willing to participate in the interview. They then provide verbal and written information and obtain written consent from those who agree. Purposive sampling is applied to ensure approximately equal sample sizes per study site, as well as variation regarding pain intensity, intervention adherence, age, gender, education, living situation, and tumour entity.

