### Data analysis

Quantitative data will be compiled and analysed using SPSS 24.0. Data will be retrieved from the SecuTrial® database. Data will be systematically examined for out of range values and data inconsistencies. As appropriate, descriptive statistics will be calculated, including means and standard deviations for interval variables and frequencies, as well as percentages for categorical variables. An intent-to-treat analysis will be applied, using a significance level of .05 [55]. Although premature withdrawal is expected to be a random process, participants who completed the study will be compared with those who did not based on demographics, treatment group and other salient variables.

#### Data analysis for aim 1

Generalized linear mixed models will be applied to determine differences between the IG and the CG analgesic side effect developments throughout the intervention. This approach allows calculation of the main group and time effects, and of group-by-time interaction. The influence of missing data on the model results will be examined using sensitivity analysis [56]. Change scores for each patient as well as Cohen’s d will be calculated for each variable of interest.

#### Data analysis for aim 2

Our quantitative analysis will use descriptive statistics to summarize PPQ/FPQ items’ distribution characteristics. Generalized linear mixed models will be applied to determine differences between the IG’s and the CG’s knowledge of cancer pain management throughout the intervention. The influence of missing data on the model results will be examined using sensitivity analysis [46]. Change scores for each patient/FC as well as Cohen’s d will be calculated for each variable of interest.

For qualitative data analysis, transcript data will be stored and analysed in ATLAS.ti 7. Field notes and audiotapes of telephone calls, home visits and interviews will serve as qualitative data to explore both the IG’s and the CG’s the learning processes concerning knowledge of cancer pain and pain self-management. Data will be analysed via interpretive description–an approach using stepwise, systematic and iterative processing of data to arrive at a meaningful description and interpretation [57].

Information from quantitative and qualitative data collection will be combined within a mixed method matrix. Qualitative and quantitative results related to each German PPQ/FPQ item will be integrated in a final synthesis [39, 58].

#### Data analysis for aim 3

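### The exclusion for a hospital stay of more than 2 weeks during the study is, as worded, met after randomisation and is not reconciled with the intent-to-treat analysis

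*Protocol article*

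**What the plan says.** The Sample and setting section introduces the exclusion list with "Participants are excluded if they (1) have cognitive dysfunction or hearing impairment", and its second item is "2) are hospitalized > 2 weeks during the study". It sits alongside characteristics that can be judged at screening, with no note that it works differently.

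The sequence of events is given in two places. Recruitment describes screening, information and written consent, then says: "Only afterwards are participants randomized to the IG or CG". The Methods paragraph of the abstract says: "After baseline evaluation, eligible participants are randomized to a 6-week intervention group and a control group".

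The Data analysis section says: "An intent-to-treat analysis will be applied, using a significance level of .05". On loss of patients it begins "Although premature withdrawal is expected to be a random process" and plans a comparison of completers with non-completers. For aims 1 and 2 it adds: "The influence of missing data on the model results will be examined using sensitivity analysis". It does not mention patients who met the hospitalisation criterion.

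**The concern.** An eligibility criterion should be decidable before allocation. A stay of more than two weeks within the study period is in practice known only later. If it is applied literally as an exclusion, randomised patients leave because of something that happened after they were assigned to an arm.

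Three features of this trial make that a practical worry:

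- A long admission is plausibly linked to deterioration, poorly controlled pain or side effects. Side effects are primary patient outcomes here and pain is secondary.
- The intervention could change how often admissions happen, in either direction. The nurses review diaries and prescriptions, and they train patients to approach clinicians when pain control is inadequate.
- The trial is unblinded and contact differs by arm. The intervention group has weekly visits or calls, while control patients are followed by a research assistant who telephones every second week between visits. The rule may therefore not be noticed or applied equally.

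At stake is whether the primary comparison remains one between the groups as randomised.

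**Working it through.** **Timing.** Eligibility check, written consent and baseline evaluation come first, then randomisation, then the six-week period. The criterion needs more than 14 days in hospital during the study. Within a 42-day period it cannot be met before day 15, by which time the patient has been allocated and has baseline data. So, as worded, the criterion acts on a post-randomisation event.

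**Against the analysis principle.** Intent-to-treat compares all randomised patients in the arm they were assigned to. A rule that takes some of them out for a later event fits that principle only if it ends participation and not membership of the analysis set. The article says neither that it does nor that it does not.

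**The one related figure.** The sample size section inflates 136 patients for 35% attrition: 136 / (1 − 0.35) = 209.2, which rounds up to the stated 210. Whether patients excluded for hospitalisation are counted within the 35% is not stated.

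**Possible size of bias.** Let m be the mean of all randomised patients in an arm, p the share removed, and D the amount by which removed patients score worse (higher) than those kept, whose mean is r.

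- m = (1 − p) × r + p × (r + D), so r = m − p × D.
- With the same D in both arms, the difference IG − CG among those kept is the true difference plus (p_CG − p_IG) × D.

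The article gives neither p nor D, so every value below is an assumption. With no true effect on a 0–10 scale:

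| Removed IG / CG | D = 1 | D = 2 | D = 3 |
|---|---|---|---|
| 5% / 5% | 0 | 0 | 0 |
| 5% / 10% | 0.05 | 0.10 | 0.15 |
| 5% / 15% | 0.10 | 0.20 | 0.30 |
| 10% / 5% | −0.05 | −0.10 | −0.15 |

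A positive value makes the intervention look worse than it is, and a negative value makes it look better. The 5% / 15% row, with 105 patients per arm, would mean 5.25 + 15.75 = 21 of 210 patients removed.

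**Benchmark.** The only planned effect on such a scale is 0.99 points for average pain. The range 0.05 to 0.30 is 0.05 / 0.99 = 5% to 0.30 / 0.99 = 30% of it. Pain is a secondary outcome here. The diary side-effect ratings also run from 0 to 10, so the shift in points carries over to them, but the article gives no planned effect for them to be compared with. No figure is offered for knowledge or self-efficacy.

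**The case against.** The strongest reply is that Sample and setting concerns participation and Data analysis governs who is analysed. On that view, exclusion means that home visits and diaries end while data already collected stay in the mixed models. Alternatively, the item may mean a long admission foreseen at screening, since the research assistants consult files and treating physicians before randomisation. Either reading is compatible with intent-to-treat. A condensed article may also leave the definition of the analysis set to the full protocol. The planned mixed models, missing-data sensitivity analysis, completer comparison (which includes treatment group) and 35% attrition allowance all help if these patients stay in the analysis.

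Much of this stands. A reader might infer that the two rules cannot both be followed. The article does not support that, because both readings above are open and no sentence says that hospitalised patients leave the analysis set. A reader might also infer that those removed are the patients with the worst outcomes. The article gives no reasons for admission, and a planned admission would also count, so this is plausible but not established.

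What remains is that the written rule says excluded and places the event during the study. The same section marks a forecast when it means one, as with estimated life expectancy. The point therefore concerns an explicit rule, not detail left out of a summary. Under the participation-only reading, outcomes after the stop would be missing for a health-related reason, which sits uneasily with the expectation that withdrawal is random. Knowledge and self-efficacy are measured only at weeks 0 and 6, so a patient who leaves early contributes only a baseline value to those analyses. The completer comparison would describe an imbalance but not restore the randomised comparison.

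**Conclusion.** The point holds as an unreconciled conflict. As worded, the hospitalisation criterion is met after allocation, and the article does not say how removing such patients squares with intent-to-treat. Followed literally, it would allow randomised patients to be dropped for an event plausibly related to both outcome and arm in an unblinded trial.

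Whether bias would arise, how large and in which direction cannot be determined from the article. It is zero with equal removal rates and equal prognosis. It is 0.05 to 0.30 points in absolute size under the assumed rates of 5% against 10–15% and a 1–3 point worse score. The upper end should not be read as an expected loss of 30% of the planned effect: nothing in the article supports those rates for outpatients followed for six weeks, and the 0.99 benchmark belongs to a secondary outcome. The case for a change rests on the wording and the low cost of correcting it, not on a demonstrated bias.

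**What to change.** Reconcile Sample and setting with Data analysis:

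1. Take hospitalisation of more than 2 weeks out of the eligibility exclusions, or reword it so that it concerns study procedures only. Which of the two suits the trial is for the investigators.
2. State that all randomised patients stay in the intent-to-treat mixed models with all data obtained.
3. Record hospitalisation of more than 2 weeks as an on-study event and report the number by arm.
4. If an analysis without these patients is wanted, label it a sensitivity analysis.

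The cost is a few sentences and a few more patients with partial data in the models. The sample size need not change if these patients are already within the 35% attrition, which should be stated. Because the criterion comes from the ongoing parent trial, patients already handled under it should be identified and counted by arm, and any data they provided kept in the analysis.
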